### Statistical analysis

Sample size: A sample size of 269 (n = 135; 135) was derived based on a moderate effect size assumption, using G power software’s formula for F-test, ANCOVA with fixed effect, main effect and main effect interaction model for 2 group comparisons. The calculated sample size also aligns with the estimate presented by Leon et al. 2009 (39). Further, assuming an attrition rate of 20%, the final sample size is n = 323 subjects randomized in a 1:1 ratio to yoga or brisk walking.Baseline characteristics will be presented using appropriate descriptive statistics. Before analysis, variable distributions will be examined to ensure that assumptions of normality are met using statistical software (SPSS, Statistical Package for the Social Sciences, Version 20.0) with the Shapiro-Wilk test. The equivalence of variance will be found using the F distribution test. Depending on the distribution of data, parametric or nonparametric tests will be performed within and between group comparisons for baseline data. The baseline characteristics of the study completers will also be compared with drop-outs. If the data will be skewed, non-parametric analysis through the Kruskal-Wallis test

Study outcomes will be compared between groups based on the intention-to-treat (ITT) principle. The change in CAIDE risk score from baseline vs. control will be analyzed using a mixed-effects model for repeated measures, adjusted for covariates as fixed effects. The covariates will be the baseline values of the covariates: age (years), education (years), sex (male vs. female), smoking status, and baseline CAIDE risk score. For each continuous endpoint, the baseline of the endpoint variable was included in the model. For genotype x intervention interaction effect, an interaction model will be created, and the influence will be evaluated through a generalized estimated equation model, wherein effect modification by the presence of ApoE 4 allele status will be analyzed by adding the group (yoga vs. walking) x time x variable interaction to the model, together with the main variable effect and variable x time and variable x group interactions. The model will also include interaction terms for treatment by month and a baseline CAIDE risk score by month. IBM SPSS 24.0 software will be used for all statistical analysis. Two-tailed tests will be used, and statistical significance will be set at a p-value < 0.05. Further, assuming an attrition rate of 20% and missing data, we also aim to conduct sensitivity analyses using the multiple imputation method. Subgroup analyses for age, gender, years of education, marital status, socio-economic class, BMI, SBP, Smoking and Alcohol status, etc.

The task of entering data will be carried out by clerical staff who have undergone training in research data entry. All participants will be assigned a participant number, and all data will be stored on an onsite server accessible only to the research team members. A range check will be performed for data values.

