**Participants:**

In total, 323 at-risk dementia subjects will be recruited from community settings through health awareness camps and door-to-door surveys across Delhi, India. Participants will be randomized into yoga or brisk-walking groups (1:1). The yoga intervention group will receive 60 contact yoga sessions per 60-min/day at the community parks, followed by continued tele-supervised home practice, further followed by at-home self-practice, and will be tested at 3-time points (baseline, 24-week and 48-week, post-randomization) to test the efficacy of the intervention. The control group will be asked to do brisk walking daily for 45 minutes at their convenience, followed by weekly telephone follow-ups. Applying the intention-to-treat principle, the primary endpoint will be the change from baseline at the 12th month in the Cardiovascular Risk Factors, Aging, and Dementia (CAIDE) Scores. Secondary outcomes will include the composite scores derived from a comprehensive neuropsychology battery, comprising the Trail Making Test, Digit Span Test, N Back, Color Trail, Animal Fluency Test, COWA (Controlled Oral Word Association Test), and Digit Symbol Substitution. The primary outcome will be analyzed using mixed-effect models for repeated measures, adjusted for covariates as fixed effects. The study has been prospectively registered (CTRI/2023/02/049746) on February 15, 2023. The protocol was conceptualized in 2021 and approved by the Institutional Ethics Committee of SVYASA. Recruitment began in February 2023 and is underway with patient enrollment.

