### Study Design

The study DERRY (Dementia Risk Reduction using yoga will be a prospective, parallel-group, single-center, and 2-arm randomized controlled trial wherein the subjects will be randomly allocated to two groups: yoga or active walking control. The protocol has been drafted following the CONSORT guidelines (Consolidated Standards of Reporting Trials) (17) (Figure 1). The study will be conducted between February 2023 and October 2024. A total of 323 adults (aged 30-65 years) with dementia risk (CAIDE score≥6) will be recruited from the community set up through door-to-door surveys and dementia awareness camps across Delhi, India. Eligible participants will be randomized into 1:1 yoga or active control groups. Primary and secondary outcomes will be assessed at baseline (before intervention) and at 24 and 48-week visits (with a 60-day window of flexibility) (see Figure 1). All participants will follow their usual medical regime during the study period. This protocol (RES/IEC-SVYASA/243/2022) has been approved by the Ethics Committee of Swami Vivekananda Yoga Anusandhana Samsthana. Interested and eligible individuals will be asked to attend an orientation session, and informed consent will be obtained from them before participation.

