## Adherence

Adherence will be calculated based on participation in sessions. The trainer will maintain the logbook in Phase 1, while individual participants will receive notepads to keep records in Phase 2. All these will be collected during follow-up assessments. Attendance rates will be calculated by dividing the number of sessions attended by the total number of sessions. Overall attendance will then be calculated by averaging all participants’ attendance rates. Attrition rates will be calculated by dividing the number of individuals who dropped out of the study by the total number of enrolled participants. The reasons cited for study dropout will also be summarized.

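### The 20% attrition allowance multiplies 269 by 1.2 instead of dividing by 0.8, so 323 randomised leaves about 258 participants, 11 short of the stated 269; the effect on power is minor.

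*Protocol article*

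**What the plan says.** The sample size paragraph under Statistical analysis gives the base figure: "A sample size of 269 (n = 135; 135) was derived based on a moderate effect size assumption". It then adds the allowance for loss: "assuming an attrition rate of 20%, the final sample size is n = 323 subjects randomized in a 1:1 ratio". The total of 323 is repeated in the Abstract ("In total, 323 at-risk dementia subjects will be recruited from community settings") and under Study Design ("A total of 323 adults (aged 30-65 years) with dementia risk (CAIDE score≥6) will be recruited").

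The Adherence section says how attrition is counted: "dividing the number of individuals who dropped out of the study by the total number of enrolled participants". The 20% assumption appears again later under Statistical analysis, where multiple imputation is planned as a sensitivity analysis. Testing is two-sided at 0.05 ("Two-tailed tests will be used, and statistical significance will be set at a p-value < 0.05"). The article gives no target power, no number for the moderate effect size and no numerator degrees of freedom.

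**The concern.** An attrition allowance should make the number left after the expected loss equal the number required. With a loss fraction *a* taken from those randomised, this means dividing the requirement by (1 − *a*). Multiplying by (1 + *a*) gives too few, because the loss then falls on the larger, inflated number. The step from 269 to 323 looks like the multiplication.

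What is at stake is the internal consistency of the trial's headline number. If 269 is the number needed and 20% are lost, 323 does not deliver it. Anyone checking the size justification can see this by simple division.

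**Working it through.** **Inputs from the article.** Requirement 269, attrition 20%, number randomised 323 (all under Statistical analysis). Attrition is dropouts divided by all enrolled (Adherence).

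**Reproducing the stated figure.**
- 269 × 1.2 = 322.8, rounded up to 323. This matches exactly.
- Starting from 135 + 135 = 270 gives 270 × 1.2 = 324, so the base used was 269.

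**The inflation that preserves the requirement.**
- 269 / (1 − 0.20) = 336.25, rounded up to 337. This is 337 − 323 = 14 more than stated.
- Check: 337 × 0.8 = 269.6.

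**What 323 delivers.**
- At 20% attrition: 323 × 0.8 = 258.4, about 258.
- Shortfall: 269 − 258 = 11, or 11 / 269 = 4.1%.
- Largest attrition that still leaves 269: (323 − 269) / 323 = 54 / 323 = 16.7%.

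**Effect on power.** This part needs assumptions, since the article does not give the settings behind 269. Power comes from the noncentral F distribution with noncentrality f² × N and two-sided alpha 0.05. The rows with 1 numerator df use two groups and one covariate. In the first three rows, f is solved so that N = 269 gives exactly the assumed target power.

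| Assumed setting | Power at 269 | Power at 258 |
|---|---|---|
| 1 df, sized for 80% (f ≈ 0.171) | 80.0% | 78.3% |
| 1 df, sized for 90% (f ≈ 0.198) | 90.0% | 88.8% |
| 1 df, sized for 95% (f ≈ 0.221) | 95.0% | 94.2% |
| 10 df, f = 0.25 | 80.0% | 77.9% |
| 1 df, f = 0.25 | 98.3% | 97.9% |

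In the four settings that make 269 the design target, the loss runs from 0.8 to 2.1 points. With 1 df and 80% power, the detectable standardised difference moves from 0.343 to 0.350.

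These settings are not identified by the article. With f = 0.25, 269 is returned by 80% power and 10 df, while 90% power and 5 df returns 270, which equals 135 + 135. The table therefore shows a range and does not reconstruct the authors' calculation.

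**The case against.** Four points can be made on the other side.

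1. **Adding 20% to the requirement may be what was meant.** This would make 323 right by convention. It does not stand. The article's own definition puts everyone enrolled in the denominator, so 20% attrition means 20% of 323.

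2. **The analysis is not restricted to completers.** Outcomes are compared by intention to treat with a mixed model for repeated measures, and Study Design schedules a 24-week visit. Dropouts with 24-week data can contribute, so 258 understates the usable information. This stands in part. The size of the offset is uncertain, because the Assessments section mentions calculating the CAIDE score only at baseline and 48 weeks. The sample size paragraph also takes no credit for partial data.

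3. **The shortfall is trivial in power terms.** This stands. It limits the seriousness of the error but does not remove the contradiction.

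4. **The power figures rest on unstated inputs.** This also stands. Only the headcounts, 258 against 269, follow from the article alone.

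A reader might go further and infer that the Discussion's statement of an adequate sample size is overturned. The article does not support that. The statement concerns the main effect of the intervention, a two-group contrast with 1 numerator df. If moderate is read as f = 0.25 (an assumption), 258 participants still give about 98% power. A reader might also object that 323 is odd and cannot be halved. That has no practical weight: 1:1 is an allocation ratio, 161 and 162 satisfy it in practice, and the varying block sizes do not guarantee exact equality even with an even total.

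**Conclusion.** The arithmetic is wrong as written. Under the article's own definition of attrition, 323 randomised with 20% lost leaves about 258 with 48-week data, 11 fewer than the 269 from which 323 was built. This conclusion uses only figures in the article, together with the ordinary reading that the allowance was meant to leave 269 after attrition.

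The consequence is minor. Power falls by about 1 to 2 points under the assumed settings, and by less if the mixed model uses 24-week data from dropouts. The error does not show that the trial is underpowered, and no design feature or analysis needs to change because of it.

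**What to change.** Keep 323 and correct the sentence in the sample size paragraph in one of two ways:

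- state that 323 randomised retains 269 participants provided attrition does not exceed 16.7%; or
- state that 20% attrition leaves about 258 participants with 48-week data, and quote the power or detectable effect at 258, giving the target power, the numerical effect size and the numerator degrees of freedom used.

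Either is a change of wording only. The second also requires rerunning the power calculation at 258, and the quoted figure will be slightly less favourable. The total of 323 in the Abstract and Study Design can stay. Raising enrolment to 337 (or 338 for two arms of 135 after attrition, from 270 / 0.8 = 337.5) would be justified only if 269 with 48-week data were a firm requirement. For a change of this size, with recruitment already under way, it is not needed.

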**Conclusion:**

To our knowledge, this is the first controlled trial to investigate the longitudinal effects of a yoga-based intervention on dementia risk reduction using the CAIDE risk score. The findings of this trial will also provide insight into a better understanding of genotype-dependent responses to yoga intervention and open up avenues for understanding the implications of gene-intervention interactions for precision prevention using yoga.

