## Discussion

This paper presents the protocol for the DERREY Dementia Risk Reduction using yoga, a 48-week prospective longitudinal intervention study to evaluate the potential of a yoga-based program for dementia risk reduction. The available evidence on the risk-reducing potential of exercise or physical activity has been primarily derived from prospective cohort studies and case-control studies with a baseline measure of physical activity and a follow-up measure from all-cause dementia observational studies (40). Results from the FINGER trial with a multidomain intervention are supportive of the effect of the multidomain intervention on dementia risk reduction in older adults (41, 42). However, the findings were derived from post-hoc analysis. To our knowledge, the present trial would be one of the pioneer trials shedding insights into the potential of a lifestyle modification-based intervention for the prospective risk reduction of dementia. The study has also been designed with an adequate sample size to effectively capture the primary outcome, i.e., change in CAIDE risk scores, the main effect of the intervention. Since the study outcome CAIDE is an estimated risk score, and similar to the major recent trials, the FINGER study, the present trial targets at-risk individuals without substantial cognitive impairment, incident dementia has not been deemed as a feasible come after one year. However, targeting at-risk participants from the general population would aid in the direct translation of the findings for potential risk reduction in a public health context. If found effective, the study findings will aid in designing further longterm trials to actuate and extend the findings to the true reduction potential of yoga for the incidence of dementia.

The secondary outcome of the study will shed light on the aspect of genetic risk-based identification of yoga-based personalized intervention. To our knowledge, very few trial information can personalize lifestyle modification approaches to mitigate dementia risk. Some studies have reported that adhering to a healthy lifestyle may modify the risk reduction associated with ApoE ε4 allele status (41). However, we could find rare evidence of intervention-based studies that shed light on this aspect.

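### The ApoE4 effect-modification analysis uses a GEE where the mixed model already planned for CAIDE would be more robust to dropout that depends on the 24-week score; a minor point, free to fix

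*Protocol article*

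**What the plan says.** The Statistical analysis section states that change in CAIDE "will be analyzed using a mixed-effects model for repeated measures, adjusted for covariates as fixed effects". For the genotype question it changes estimator: "the influence will be evaluated through a generalized estimated equation model". Effect modification by ApoE4 is to be tested by "adding the group (yoga vs. walking) x time x variable interaction to the model", together with the lower-order terms. It continues: "The model will also include interaction terms for treatment by month and a baseline CAIDE risk score by month". The article gives no working correlation, weighting or missing-data assumption for the GEE.

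The sample-size paragraph states: "assuming an attrition rate of 20%, the final sample size is n = 323 subjects". On missing data the analysis text adds: "assuming an attrition rate of 20% and missing data, we also aim to conduct sensitivity analyses using the multiple imputation method".

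The abstract's conclusion says the findings will "provide insight into a better understanding of genotype-dependent responses to yoga intervention", and the Discussion says: "The secondary outcome of the study will shed light on the aspect of genetic risk-based identification of yoga-based personalized intervention".

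On timing, the Study Design and Primary outcome sections and Table 1 place CAIDE at baseline, 24 and 48 weeks. The Assessments section has the score calculated at baseline and 48 weeks only.

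**The concern.** One outcome, measured on the same people, is to be analysed by two estimators that treat dropout differently. A correctly specified likelihood mixed model uses the 24-week score of those who later leave, so it remains valid when leaving depends on that score. An unweighted GEE does not have this property in general. With an independence working correlation, the 48-week means rest only on those still present, apart from covariate adjustment.

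The three-way term is a difference of differences over four cells. If leaving is tied to the 24-week score in one cell and not in the others, the selection does not cancel and appears as a genotype-dependent response. The article gives no reason for the change of estimator, and the mixed model can carry the same interaction terms.

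**Working it through.** **Attrition figure.** The plan's 323 is 269 × 1.20 = 322.8, rounded up. With 20% lost, 323 × 0.80 = 258.4 participants have a 48-week score. Whether 269 should instead be divided by 0.80 is a separate matter.

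**Set-up.** From the article: 1:1 allocation, 20% dropout, scores at 24 and 48 weeks, and a model with group, ApoE4, their interaction and baseline CAIDE, each by visit. Assumed, because the article does not give them: 30% carriers, residual SD 1, residual correlation r of 0.5 to 0.8 between the two visits, and a dropout slope of 1 on the logit scale per SD. With B the standardised baseline and G = 1 for yoga:

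- 24 weeks: Y1 = -0.3B - 0.25G + e1
- 48 weeks: Y2 = -0.3B - 0.5G + e2, with corr(e1, e2) = r

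The true ApoE4 interaction is 0. Dropout occurs after week 24, with its intercept set to give 20% overall. Very large samples (400,000 or more) were used, so the results show bias, with simulation error of about 0.01 SD or less.

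**Mechanism.** Under independence, the bias in a cell's 48-week mean is r × (mean of e1 among those who stay). When dropout depends on Y1 in yoga carriers only, that mean is about -0.175 in their cell and 0 in the other three. The interaction bias is then about r × (-0.175): -0.09 for r = 0.5, -0.12 for r = 0.7 and -0.14 for r = 0.8. Direct fits gave -0.09, -0.12 to -0.13, and -0.14. Across runs of this scenario the range is about -0.09 to -0.15.

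**Bias in the 48-week ApoE4-by-group interaction (SD units; r = 0.5 to 0.7)**

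| Dropout depends on | GEE, independence | GEE, estimated correlation | Maximum likelihood |
|---|---|---|---|
| nothing, or baseline CAIDE only | about 0 | about 0 | about 0 |
| 24-week score, same in all cells | about 0 | about 0 | about 0 |
| 24-week score, differing by arm only | about 0 | about 0 | about 0 |
| 24-week score, yoga carriers only | -0.09 to -0.13 | about 0 | about 0 |
| 24-week score, opposite directions across arm × genotype (extreme) | -0.34 to -0.47 | -0.02 to -0.03 | about 0 |

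**Scale.** With 258.4 completers and 30% carriers, each arm has 258.4 × 0.5 × 0.3 = 38.8 carriers and 258.4 × 0.5 × 0.7 = 90.4 non-carriers. The interaction has SE = √(2/38.8 + 2/90.4) = √0.0737 = 0.27 SD. The moderate-scenario bias is therefore 0.09/0.27 = 0.33 to 0.15/0.27 = 0.56 of one standard error. With 25% carriers the SE is 0.29 SD.

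**Precision.** In a separate simulation at trial size (25% carriers, about 17% dropout after week 24) the SE was about 0.28 SD for the independence GEE and 0.26 to 0.28 SD for the mixed model. The change costs no precision.

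**If CAIDE has no 24-week value.** One post-baseline score per person remains. GEE and mixed model with the same covariates then give essentially the same estimate, and the mixed model has no advantage.

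**The case against.** A reader might infer that the GEE requires data missing completely at random, so that 20% attrition by itself distorts the genotype result. The article does not support that. Dropout may depend on anything in the model, and group, ApoE4 and baseline CAIDE by month all appear to be in it. The first three rows of the table show no interaction bias. Neither independence nor the absence of weighting is stated in the article; both are details commonly left to an analysis plan, and with an estimated correlation the bias almost disappears. Nothing suggests that dropout will follow the yoga-carrier pattern. All of this stands, and it limits the point to a possible bias under a particular pattern and implementation.

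The multiple imputation is worded broadly enough to cover the GEE. That stands in part: it is only a sensitivity analysis and is not tied to the GEE, so the headline genotype estimate would still be the unprotected one.

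One could add that GEE with robust standard errors is a recognised choice for a bounded sum of category points. That is true, but the plan already models the same score with a mixed model, so it gives no reason to switch here.

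Finally, the listed secondary outcomes are CAIDE components and cognitive scores, and the genetic work is described as exploring associations. The Discussion sentence does not make this a main analysis. That stands, and it lowers the priority.

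**Conclusion.** The point holds as a minor improvement to a stated method. The GEE leaves the ApoE4 interaction less protected than the planned mixed model in one circumstance: dropout depends on the 24-week CAIDE score, the dependence differs across arm-by-genotype cells, and the working correlation is independence. Under the assumed carrier share, correlations and dropout slope, the bias is then about -0.09 to -0.15 SD, against near 0 for a mixed model. The larger figures in the table belong to a deliberately extreme pattern and should not be read as expected.

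The documents do not show that the genotype result will be biased, and the primary yoga-versus-walking comparison is untouched. The conclusion also rests on CAIDE being scored at 24 weeks. Three places in the article say so, and the time interactions on a change score presuppose it, but the Assessments section says otherwise.

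**What to change.** Estimate effect modification in the primary mixed model: add ApoE4, ApoE4 × visit, ApoE4 × group and ApoE4 × group × visit to the existing fixed effects, with an unstructured covariance. Report the 48-week yoga-minus-walking difference in carriers and in non-carriers, and the interaction with its confidence interval.

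If GEE is kept, specify a non-independence working correlation and apply it to multiply imputed or inverse-probability-weighted data, stating that this is the main genotype analysis and not only a sensitivity check.

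In either case, reconcile the Assessments section with Study Design, Primary outcome and Table 1 on whether CAIDE is calculated at 24 weeks.

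The cost is one or two sentences in the analysis section and one correction of timing. The first option needs no extra data and loses no precision.
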